2. HIV testing with prompt initiation of both antiretrovirals and TB preventive treatment for HIV-infected contacts according to current South African guidelines,
3. Preventive therapy for tuberculin skin test-positive, HIV-negative **and** HIV-infected household contacts without active TB disease;
4. A three-month supportive follow-up visit to confirm treatment receipt, and assist those who have either not accessed care and treatment; or who have experienced problems with their treatment; or who have developed symptoms of TB in the interim.

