**Sputum Collection**

To avoid bias related to collecting better quality sputum samples from symptomatic patients, we will collect one spot sputum sample from all household members capable of producing a sputum sample, before we ask about TB symptoms. Prior to producing a sputum specimen household members will be asked to drink a cup of water and rinse out their mouths, then take four deep breaths prior to giving a good cough effort. If small volumes of sputum are obtained, we will allow up to three hours for the collection of a spot sputum specimen. This specimen will be subjected to Xpert MTB/Rif (or the at time-of-study current version of the usual first line TB lab test in the public sector) and liquid mycobacterial culture at public sector laboratories. Single sputum specimens will be at least 3ml and at the lab will be mixed with decontaminant as per standard operating procedures in the two public sector laboratories we will send specimens to - then split into two: Xpert MTB Rif (with subsequent addition of buffer) and immediate liquid culture in the MGIT automated system as per current protocols in public sector mycobacterial laboratories. We will record the cycle threshold number of the Xpert and the time-to-positive in liquid culture. Sputum samples will be immediately stored and transported in coolboxes at 4ºC to public sector laboratories for testing. Anyone who tests positive for *M tuberculosis* will be immediately referred to their chosen public sector clinic for TB treatment initiation with a clear referral letter. For those who are Xpert MTB/Rif negative, HIV-negative and over 5 years of age a tuberculin skin test will be performed with the needle of the syringe parallel to the long axis of the arm at this initial visit and read 48 – 72 hours later using the ball-point pen to mark the widest transverse diameter measured with the reverse calliper method in millimetres. No induration will be documented as 0mm.

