**Follow-up household visit (1week after baseline household visit)**
Xpert MTB results and results of laboratory HIV testing (and CD4 counts and HbA1C as appropriate) will be communicated to participants by study staff including registered nurses at a follow-up household visit approximately one-week after the baseline assessment is completed. Participants with microbiologically-confirmed tuberculosis or diagnosed with HIV will be supported to attend their nearest local primary care clinic to register for ongoing care and treatment.

Participants who are older than 5 years of age or test HIV-negative and whose sputum tests are negative for TB and whose tuberculin skin test is negative will be dispensed the first month of IPT by study nurse and then referred for ongoing preventive treatment at their local clinics with a clear referral letter that includes all results. Additionally all those participants who are less than 5 years of age or are HIV-positive and sputum tests are negative for TB will be dispensed the first month of isoniazid preventive therapy by study nurses, Linkage to care will be confirmed by collection of referral cards at study facilities by study staff. Home tracing to encourage re-entry to care will be undertaken on three occasions for participants who do not attend clinics within 2 weeks of referral.

Should any liquid TB culture be resulted positive after this visit, a visit will be made to the few anticipated households from where this result was taken to inform the patient and refer him/her for TB treatment.

| **Age of household member** | **HIV status** | **TST Required** | **Active TB disease** | **TB HH contact** | **IPT initiated** | **Study procedure** |
| --- | --- | --- | --- | --- | --- | --- |
| Child < 5 years | POSITIVE on ART or not | NO | NO | YES | YES | Initiate 1 month IPT |
| Child ≥5 years, adult or adolescent | POSITIVE on ART or not | NO | NO | YES | YES | Initiate 1 month IPT |
| Child < 5 years | NEG | NO | NO | YES | YES | Initiate 1 month IPT |
| Child ≥5 years, adult or adolescent | NEG | YES | NO | YES | YES | Initiate 1 month IPT |

Table 1. IPT initiation for household contacts without TB symptoms

*Final intervention household visit (3 months after baseline household visit)*

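### The rule for dispensing the first month of isoniazid is stated with conditions that do not match: the text requires negative sputum tests and ignores symptoms, while Table 1 requires no symptoms and no active disease and ignores sputum.

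*Protocol*

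**What the plan says.** The relevant act is a study nurse handing over the first month of isoniazid about a week after the baseline household visit (Protocol, Trial Procedures, Follow-up household visit).

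The text gives two dispensing sentences. One concerns "Participants who are older than 5 years of age or test HIV-negative and whose sputum tests are negative for TB" and adds a tuberculin result. The other says that "participants who are less than 5 years of age or are HIV-positive and sputum tests are negative for TB will be dispensed" the first month. Neither mentions symptoms or active disease.

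The table that follows is captioned "Table 1. IPT initiation for household contacts without TB symptoms". Each of its four rows has active TB disease marked NO and isoniazid marked YES. It has no sputum column and no row for a contact with symptoms.

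The Executive Summary (component 3 of the intervention) describes preventive therapy for "household contacts without active TB disease", without saying whether symptoms, sputum or both establish that state. Study Definitions does not define the term either.

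On sputum, the section Sputum Collection asks for "one spot sputum sample from all household members capable of producing a sputum sample" and sends it for both Xpert and liquid culture. The TB results listed for the one-week visit are Xpert only ("Xpert MTB results and results of laboratory HIV testing"). The same section then provides for late cultures: "Should any liquid TB culture be resulted positive after this visit, a visit will be made to the few anticipated households", so that the contact can be told and referred.

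**The concern.** A nurse at the one-week visit has two eligibility statements in one section, and each omits what the other requires. The safety question is whether a contact with symptoms and an outstanding culture can leave the visit with single-drug isoniazid under the protocol's own wording. The delivery question is whether two teams, one working from the text and one from the table, would treat the same young child differently.

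The ambiguity also reaches two other sections. Adverse events classes treatment started in error after a misread TB result as serious, and error is hard to judge without a single rule. Outcomes plans an exploratory comparison by receipt of isoniazid, and that exposure is harder to describe if eligibility was applied in different ways.

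**Working it through.** No arithmetic applies to the rule itself, so the check sets the statements side by side and then runs contacts through them.

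| Condition | Dispensing text | Table 1 | Executive Summary, component 3 |
|---|---|---|---|
| TB symptoms | not mentioned | must be absent (caption) | not mentioned |
| Active TB disease | not mentioned | NO in every row | must be absent, not defined |
| Sputum tests | must be negative | no column | not mentioned |

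**Contact A: HIV-positive adult with a cough, Xpert negative, culture pending.** The text dispenses. Table 1 does not cover this person, because its caption limits it to contacts without symptoms. The baseline questionnaire records symptoms (Trial Procedures, initial household contact), but no section says what they mean at the one-week visit. The next symptom screen that leads to investigation is at about three months, after the first month's supply has been handed over. A child under 5 with symptoms and a negative Xpert is in the same position.

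**Contact B: HIV-negative child under 5, no symptoms, unable to produce sputum.** Table 1 initiates isoniazid. What the text does depends on how its 'or ... and' clause is read:

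- If the sputum condition applies to both groups, the child has no negative result and the text does not reach the child.
- If it applies only to HIV-positive contacts, the text reaches every child under 5. It then sets no sputum, symptom or disease condition for that group, so it still differs from Table 1.

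**Contact C: HIV-positive or under 5, no symptoms, Xpert negative.** Text and table agree. Culture may be pending here too.

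**What counts as negative sputum tests.** The specimen goes to two tests, and only Xpert is listed as reported at this visit. If the phrase means Xpert alone, Contact A is dispensed isoniazid with culture outstanding. If it includes culture, the condition cannot be confirmed at one week for anyone whose culture is still running. The timing of the visit and the late-culture provision make the first meaning more likely, but the text does not state it.

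**Late-positive culture.** The provision is a further visit to inform and refer. It is silent on isoniazid already dispensed.

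**The case against.** The strongest reply is that text and table sit together and can be read cumulatively: the caption restricts the scheme to contacts without symptoms, and negative sputum helps establish that active disease is absent. The Executive Summary also ties preventive treatment of HIV-infected contacts to national guidelines, which are not in the document. Pending culture is anticipated, affects contacts without symptoms equally, and has a referral visit attached.

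Part of this stands. A reader might infer that text and table give opposite instructions, and they do not. Table 1 has no row refusing isoniazid; in Contact A, and in Contact B on the first reading, one source dispenses and the other does not reach the contact. Pending culture by itself is not a conflict between text and table. The cumulative reading, however, is stated nowhere, and the dispensing sentence for under-5s and HIV-positive contacts is worded to take in all who meet its conditions. A nurse who follows it literally dispenses to Contact A.

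A reader might also infer that isoniazid in undiagnosed disease would lower later smear or culture yield in one arm and so bias the confirmed-TB version of the primary outcome. The documents do not support this. No section says isoniazid has that effect. Baseline sputum is collected before any isoniazid is given. Study Definitions counts incident confirmed cases only from specimens taken at least 2 months after the baseline contact, so a late-positive baseline culture is not an outcome event. The primary outcome is also measured irrespective of diagnostic method.

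**Conclusion.** The mismatch is real. The text, Table 1 and the Executive Summary set different conditions for the same act, and no other section resolves them. The text as written lets a symptomatic, Xpert-negative contact with culture pending receive isoniazid alone. The example of the child without sputum holds on one reading of an ambiguous clause. The finding concerns safety and consistent delivery.

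Its size is not known from the documents. A reader might try to count those affected. Assuming 1,200 intervention households, 4.5 to 5.5 contacts each, and 10 to 20% with symptoms gives 1,200 x 4.5 x 0.10 = 540 to 1,200 x 5.5 x 0.20 = 1,320. The symptom share is not in the protocol, and the count wrongly includes Xpert-positive contacts. It is therefore not an estimate of the group at issue (symptomatic, Xpert-negative, later culture-positive). The protocol itself expects few households with late-positive cultures.

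Which condition is clinically right is not judged here.

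**What to change.** Reconcile the dispensing sentences, the Table 1 caption and columns, and component 3 of the Executive Summary into one eligibility statement for the one-week visit, with the clinical rule chosen by the sponsor's clinicians. The statement should say:

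- how TB symptoms count;
- how a sputum result that could not be obtained counts, for children under 5 in particular;
- whether negative sputum tests means Xpert alone, and how a pending culture counts;
- what is to be done about isoniazid already dispensed if culture later turns positive.

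The 'or ... and' clause should be split so that it is clear to which group the sputum condition applies. The same rewrite should settle a separate contradiction: the text dispenses to one group on a negative tuberculin test, while the Executive Summary names tuberculin-positive contacts.

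The cost is amendment wording and a short staff briefing. No visits or tests are added. Symptom status at baseline and culture results are already recorded, so new data items are not essential.

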**Objectives**:

Primary trial outcomes are:

1. Comparison between trial groups of TB FREE SURVIVAL from two months after randomisation – to the final ascertainment visit among all household members identified at baseline – a total of 13 months. We will measure this in two ways; firstly, including all cases of where TB was diagnosed or multi drug TB treatment started, irrespective of the diagnostic method used and secondly, including only those with a hard copy of a laboratory confirmation of TB.

*Secondary trial outcomes*

1. Comparison between trial groups of the proportion of TB cases with diagnostic delay (defined as number of days between onset of symptoms and diagnosis of anti-tuberculosis treatment) among household members identified at baseline and diagnosed with TB between baseline and month 15
2. Comparison between trial groups of the prevalence of TB infection measured by tuberculin skin test reactivity >10mm at month 15 among household children identified at baseline and aged under 14 years of age.
3. Comparison between trial groups of the prevalence (reported as a percentage of those tested) of previously undiagnosed and untreated HIV infection among household members identified at baseline and again at month 15.
4. Comparison between trial groups of the cumulative incidence of all-cause mortality among all household members identified at baseline between baseline and month 15.
5. Comparison between trial groups of the cumulative incidence of TB- and HIV-related non-traumatic mortality among all household members identified at baseline between baseline and month 15.
6. Estimation of the cost-effectiveness of the intensified housed TB and HIV case-finding and prevention activities compared to the enhanced standard of care from a societal perspective. This will include comparisons of household costs and of quality of life of household members in the IHF and enhanced standard of care arms.

*Exploratory outcomes*

1. Cohort analysis of the incidence of bacteriologically-confirmed, and all-forms of tuberculosis among intervention group household members receiving and not receiving isoniazid preventive therapy, stratified by HIV serostatus.
2. Cohort analysis of the proportion of household members in the intervention group with previously undiagnosed HIV infection identified at baseline who successfully initiate antiretroviral therapy by month 15.

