All intervention households will be visited once at approximately three months after the initial assessment. This visit will be offered because our previous data suggests that a significant proportion of household members with either TB, or HIV, diagnosed at the baseline household visit, do not access care or treatment. Patients not accessing TB treatment, ART or IPT care will be reassessed and assisted to start appropriate treatment, with study staff attempting to overcome access barriers identified by this group. In addition, we will reassess whether those with hypertension or those diagnosed with type 2 diabetes mellitus were started on appropriate therapy and are at this visit controlled or have a plan for future care. Household members requiring other assistance or care will receive supported access to their local health facility or to the Department of Social Development to access social grants. Moreover, at this visit a TB symptom screen on all available household members not on TB treatment will be done, with investigation of those with symptoms, using Xpert and TB culture. We will not visit the household again to interview household members not present at this single final intervention visit.

All visits will be recorded including the number and level of staff members and the purpose and duration of the visit.

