## Outcomes

*Primary trial outcomes*

1. Comparison between trial groups of TB FREE SURVIVAL from two months after randomisation – to the final ascertainment visit among all household members identified at baseline – a total of 13 months. We will measure this in two ways; firstly, including TB irrespective of the diagnostic method and secondly, including only bacteriologically-confirmed cases of TB.

*Secondary trial outcomes*

1. Comparison between trial groups of the incidence of all-forms of TB over months 2-15 among household members identified at baseline
2. Comparison between trial groups of the proportion of TB cases with diagnostic delay (defined as number of days between onset of symptoms and diagnosis of anti-tuberculosis treatment) among household members identified at baseline and diagnosed with TB between baseline and month 15
3. Comparison between trial groups of the prevalence of TB infection measured by tuberculin skin test reactivity >10mm at month 15 among household children identified at baseline and aged under 14 years of age. Analysis will be done overall and stratified by age.
4. Comparison between trial groups of the prevalence (reported as a percentage of those tested) of previously undiagnosed and untreated HIV infection among household members identified at baseline and again at month 15.
5. Comparison between trial groups of the cumulative incidence of all-cause mortality among all household members identified at baseline between baseline and month 15.
6. Comparison between trial groups of the cumulative incidence of TB- and HIV-related non-traumatic mortality among all household members identified at baseline between baseline and month 15.
7. Estimation of the cost-effectiveness of the intensified housed TB and HIV case-finding and prevention activities compared to the enhanced standard of care from a societal perspective.

*Exploratory outcomes*

1. Cohort analysis of the incidence of bacteriologically-confirmed, and all-forms of tuberculosis among intervention group household members receiving and not receiving isoniazid preventive therapy stratified by HIV serostatus.
2. Cohort analysis of the proportion of household members in the intervention group with previously undiagnosed HIV infection identified at baseline who successfully initiate antiretroviral therapy by month 15.

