# Study Definitions

**Households:** Physical dwelling structures comprising of all rooms under a contiguous roofed area linked by doorways or windows through which air can pass or potentially can pass.

**Household members:** All individuals who shared household airspace for lengthy periods – either slept overnight at least once, or shared at least two meals in the same household as the index case - in the 14 days prior to the index case’s diagnosis of TB

**Incident bacteriologically-confirmed TB** will be defined by a household contact who has documented evidence of at least one of any of the following: sputum smear positive for acid-fast bacilli; or culture with growth of Mycobacterium tuberculosis confirmed on speciation; or positive Xpert MTB/Rif result; or histology or cytology suggestive of TB, regardless of whether TB treatment was initiated. We will restrict incident cases to those diagnosed on a specimen taken at least 2 months after the initial baseline household contact.

**Incident bacteriologically unconfirmed TB** will be defined by a household contact without bacteriologically-confirmed TB but who has at least one of the following: TB treatment registers, or patient held TB treatment cards indicate TB treatment was initiated; or either died or was discharged from hospital with a diagnosis of TB without laboratory confirmation.

**All forms of TB** will be defined in individuals with either bacteriologically-confirmed, or bacteriologically-unconfirmed TB.

**Prevalent *Mycobacterium tuberculosis infection*** will be defined by the presence of skin induration reaction measured to be >10mm using technique recommended by the International Union Against Tuberculosis and Lung Disease at 48-72 hours after subdermal injection of 2 TU in 0.1 ml PPD RT23/Tween 80 in children younger than 7 years of age.

**Prevalent previously undiagnosed HIV infection** will be defined by household members who, at month 15 assessment, test positive for HIV using a serial rapid diagnostic test algorithm infection, having reported never previously tested positive for HIV.

**Prevalent previously undiagnosed and untreated HIV infection** will be defined by household members who, at month 15 assessment, test positive for HIV using a serial rapid diagnostic test algorithm infection and report not currently taking antiretroviral therapy.

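### The primary TB event is defined inconsistently, so TB already found before month 2 can be counted as a new event

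*Protocol*

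**What the plan says.** **Executive Summary, primary outcomes.** TB-free survival runs from two months after randomisation to the final visit, 13 months in all. The first version is described as "including all cases of where TB was diagnosed or multi drug TB treatment started, irrespective of the diagnostic method used".

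**Outcomes section.** The window is the same: "Comparison between trial groups of TB FREE SURVIVAL from two months after randomisation". The two versions are "firstly, including TB irrespective of the diagnostic method and secondly, including only bacteriologically-confirmed cases of TB". Treatment start is not mentioned.

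**Study Definitions.** For confirmed TB: "We will restrict incident cases to those diagnosed on a specimen taken at least 2 months after the initial baseline household contact". Unconfirmed TB "will be defined by a household contact without bacteriologically-confirmed TB but who has at least one of the following", and the first listed criterion is "TB treatment registers, or patient held TB treatment cards indicate TB treatment was initiated". No date limit is attached to the unconfirmed definition. All forms of TB is the union of the two.

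**Trial Procedures, final intervention visit at about three months.** The stated reason for the visit is that "a significant proportion of household members with either TB, or HIV, diagnosed at the baseline household visit, do not access care or treatment". At the visit, "Patients not accessing TB treatment, ART or IPT care will be reassessed and assisted to start appropriate treatment". Household members not on TB treatment are also screened for symptoms, and those with symptoms are tested by Xpert and culture.

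**Non-intervention group.** After the call at about one week, these households have no further contact until the outcome visit.

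**Statistical analysis, analysis populations.** The primary population (cohort A) is everyone listed at baseline with information at the final visit. Contacts known to have TB at baseline are not removed.

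**The concern.** The window opens at month 2 so that events represent TB arising after the intervention has acted. That works only if each episode has one date, set by the same rule in both arms. Here the same contact can be an event or a non-event depending on which section is applied.

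The contact most exposed is one whose TB the intervention found at baseline, who did not reach care, and who started treatment after the month-3 visit. Counting that contact as new TB scores successful detection followed by late linkage as a failure of prevention. Few events are expected, so a small number of such classifications matters.

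**Working it through.** **Timing.** The baseline household visit takes place within 14 days of recruitment, and the linkage visit about three months after it. The linkage visit therefore falls about 3.0 to 3.5 months after recruitment, inside the 2 to 15 month window.

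**Clock.** The Executive Summary and the Outcomes section count two months from randomisation. Study Definitions counts two months from the baseline household contact. In the intervention arm this can shift the limit by up to 14 days. In the control arm no such contact takes place, so the limit has no defined starting point.

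**How each type of contact is classified.**

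- *Laboratory-confirmed at baseline, first treated after the month-3 visit, no new specimen.* An event under the Executive Summary, through treatment start. Under Study Definitions, read strictly, not an event: the specimen is too early for the confirmed definition, and the unconfirmed definition is closed to anyone with confirmed TB.
- *Diagnosed clinically before month 2, never laboratory-confirmed, treatment on record.* Meets the unconfirmed definition whatever the treatment date.
- *Found at baseline, untreated, symptomatic at month 3 and positive on a new specimen.* The specimen was taken more than two months after baseline, so the contact literally meets the confirmed definition. Both versions of the primary outcome are affected.

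**Expected events.** The protocol states no event count, so it is derived.

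- Contacts per arm: 1,200 households × 5.5 = 6,600. The sample-size section gives 2,400 households in total; 1:1 allocation is assumed.
- Rate: the sample-size section takes the mean of the district incidences and names Capricorn (371) and Matlosana (937): (937 + 371)/2 = 654 per 100,000.
- Control events: 6,600 × 0.00654 × 13/12 = 46.8.
- Intervention events, taking the 30% difference as a rate ratio of 0.70: 46.8 × 0.70 = 32.7.
- Difference: about 14 events, or 14.0/6,600 = 0.21% of intervention contacts.

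**Range for that threshold.** With 686 and 371 (mean 528.5) it is 11.3 events; at 937 it is 20.1. The stated 80% power is not reproduced at 654 per 100,000: power is about 35% with 0.3 as a coefficient of variation and 17 to 18% with it as an intracluster correlation. That is a separate matter, but the protocol may have meant a higher household rate that it does not state. At about 2,100 per 100,000, which would give 80% on the first reading, the threshold is 6,600 × 0.021 × 13/12 × 0.30 = 45 events.

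**Illustration, control events fixed.** Added events = 6,600 × baseline TB prevalence × share first treated after month 2. Both inputs are assumed; the protocol gives neither.

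| Prevalence | Late share | Added | Observed ratio |
|---|---|---|---|
| 0.5% | 10% | 3.3 | (32.7 + 3.3)/46.8 = 0.77 |
| 1% | 10% | 6.6 | 0.84 |
| 1% | 20% | 13.2 | 0.98 |
| 2% | 20% | 26.4 | 1.26 |

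**Illustration, control events not fixed.** At 1% prevalence the control arm also has 66 contacts with TB at baseline. Suppose 13.2 events are added to the intervention arm, giving 45.9. If 20% of the 66 surface after month 2, the ratio is 45.9/(46.8 + 13.2) = 0.77. If 50% surface, it is 45.9/(46.8 + 33.0) = 0.58. These shares are also assumed.

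**The case against.** A reader might infer that the intervention's own linkage visit creates primary events in one arm only and so biases the trial against the intervention. The documents do not support that, for four reasons.

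First, Study Definitions is the more specific text, and read strictly it keeps out a laboratory-confirmed baseline case on treatment start alone. Baseline detection is by Xpert and culture, so most baseline cases would be confirmed. Second, the visit is confined to one arm but the event is not: a control contact diagnosed before month 2 and treated later meets the same Executive Summary wording. Third, control contacts with undetected TB at baseline count as events when diagnosed after month 2, which pushes the comparison the other way. Fourth, the protocol provides supported clinic attendance after the one-week visit and up to three home-tracing attempts for those who do not attend within two weeks. Both reduce late starts, and the protocol's remark on failure to reach care pools TB with HIV.

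It can also be said that the outcome visit records when TB was diagnosed, which suggests dating by diagnosis, and that detailed dating rules often sit in the analysis plan.

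All of this stands against a claim of one-directional bias. It does not remove the conflict. The protocol fixes the event in three places with different content and gives none of them precedence, and the second and third contacts listed above get in under Study Definitions itself.

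**Conclusion.** The primary event rule is internally inconsistent and can count TB evidenced before month 2 as a new event. At 654 per 100,000, about 14 misdated intervention events would equal the entire targeted difference, with control events held fixed, 1:1 allocation and a rate ratio of 0.70. The threshold is 11 to 20 across the district rates in the protocol. The observed ratios of 0.77 to 1.26 in the table are illustrations on assumed prevalence and late-start share, and leave out the opposing effect of prevalent control TB. The documents fix neither the size nor the net direction of bias. They do leave open which events count, and that should be settled before unblinding.

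**What to change.** Use one event definition in the Executive Summary, the Outcomes section and Study Definitions, with one clock for both arms, starting at randomisation.

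- Date each episode, confirmed or not, by its first positive specimen or recorded diagnosis, and by treatment start only if neither exists.
- State that a later treatment start or repeat positive specimen belonging to an untreated episode first evidenced before month 2 is not a new primary event.
- Apply the same month-2 limit to the unconfirmed definition.
- Add a sensitivity analysis counting all TB from randomisation in both arms. Early detection is systematic in the intervention arm only, so dating by first evidence will remove prevalent cases mainly there, and this analysis shows how much the result depends on that.

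The cost is definition wording and one analysis, with no change to visits or care. Contacts' dates should be obtainable from the baseline sputum results, the one-week and three-month visits, and the final outcome visit, which records when TB was diagnosed. The downside is slightly fewer primary events.
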